### Study Treatments

For patients randomised to paramedic cooling:

- Standard advanced cardiac life support

- Advanced Airway (Endotracheal Tube/Laryngeal Mask Airway) and ventilation with 100% oxygen

- Infuse 20 mL/kg cold fluid via IV stat during CPR

- Measure temperature using tympanic probe

- If temperature > 34.5°C, infuse further 10 mL/kg stat

- After ROSC, infuse further 10-20 mL/kg (to a maximum of 2 litres total fluid) ice-cold saline

- If shivering occurs post resuscitation, administer midazolam 2-5 mg IV and pancuronium 8 mg (Victoria only)

For patients randomised to hospital cooling:

- Standard advanced cardiac life support

- Advanced Airway (Endotracheal Tube/Laryngeal Mask Airway) and ventilation with 100% oxygen

- Measure temperature using tympanic probe

- Insert IV line and administer drugs as per protocol

- Fluid challenge with standard temperature saline only as per current patient care guideline

- Post resuscitation: midazolam 1-5 mg only to maintain intubation as needed

- Pancuronium 8 mg only if intubation unable to be maintained with midazolam (Victoria only)

After arrival at the Emergency Department, all patients receive standard care which may include cooling to 33°C for 24 hours.

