**Methods/Design:**

This paper describes the methodology for a definitive multi-centre, randomised, controlled trial of paramedic cooling during CPR compared with standard treatment. Paramedic cooling during CPR will be achieved using a rapid infusion of large volume (20-40 mL/kg to a maximum of 2 litres) ice-cold (4°C) normal saline.

The primary outcome measure is survival at hospital discharge. Secondary outcome measures are rates of return of spontaneous circulation, rate of survival to hospital admission, temperature on arrival at hospital, and 12 month quality of life of survivors.

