Given these supportive laboratory and preliminary clinical data, we are conducting a definitive multi-centre, randomised, controlled trial of paramedic cooling during CPR compared with usual paramedic practice. We aim to determine whether paramedic cooling during CPR using a rapid infusion of large volume (20-40 mL/kg) ice-cold (4°C) normal saline improves outcome compared with standard treatment in patients who are being resuscitated from out-of-hospital cardiac arrest.

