## Methods/Design

The RINSE trial is a prospective, multi-centre, randomised, single blinded, controlled trial conducted by the ambulance services of Victoria, Western Australia and South Australia.

In the treatment arm, paramedics will undertake immediate cooling on arrival and during cardiac arrest, using a large volume (20 mL/kg up to 2 litres) intravenous bolus of ice-cold saline. The saline infusion will be continued after return of circulation and en-route to hospital. In the control arm, patients will receive standard paramedic care, which includes the administration of normal saline at ambient temperature and will be cooled after arrival at the hospital (the current standard of care in ambulances in Australasia).

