There is an urgent need to improve outcomes from out-of-hospital cardiac arrest. The RINSE trial will test the effect of administration of a bolus of 20 mL/kg of ice cold saline during CPR on patient survival. If this simple, inexpensive treatment is found to improve patient outcomes it will be an important prehospital intervention globally.

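### The cold-saline volume is stated inconsistently, and the weight-based steps do not fit the 2-litre maximum above 66.7 kg on either reading of that maximum

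*Protocol article*

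**What the plan says.** Five places in the protocol article describe the volume of ice-cold saline in the paramedic-cooling arm.

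- **Abstract, Methods/Design:** "large volume (20-40 mL/kg to a maximum of 2 litres) ice-cold (4°C) normal saline".
- **Background, closing paragraph (the aim):** "using a rapid infusion of large volume (20-40 mL/kg) ice-cold (4°C) normal saline". No maximum is given.
- **Methods/Design, opening description of the treatment arm:** "using a large volume (20 mL/kg up to 2 litres) intravenous bolus of ice-cold saline", followed by "The saline infusion will be continued after return of circulation and en-route to hospital", with no volume attached to the continuation.
- **Methods/Design, Study Treatments:** 20 mL/kg during CPR; then "If temperature > 34.5°C, infuse further 10 mL/kg stat"; then "After ROSC, infuse further 10-20 mL/kg (to a maximum of 2 litres total fluid) ice-cold saline". The 2-litre figure is printed on the last of these only.
- **Discussion, closing paragraph (what the trial will test):** "administration of a bolus of 20 mL/kg of ice cold saline during CPR".

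**The concern.** The infused volume is part of what is being randomised, so the article should define it in one way. The aim describes a 20-40 mL/kg infusion, while the closing statement of what is tested describes a 20 mL/kg bolus. The operational steps can run higher than either.

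The 2-litre figure adds a second problem. It limits total volume and so bears on safety, but it sits beside one step of three, and weight-based amounts reach it at ordinary-looking adult weights. A reader cannot tell whether the earlier steps are to be cut short by it, or how much of the last step is deliverable.

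Two things are at stake: whether adherence to the assigned treatment can be judged against one definition in three ambulance services with differing procedures, and whether the result can be attached to a clearly stated intervention. The sample size is not affected.

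**Working it through.** **Inputs.** All volumes come from the article: step 1, 20 mL/kg; step 2, 10 mL/kg if the temperature is above 34.5°C; step 3, 10-20 mL/kg after ROSC; maximum 2 litres (2000 mL). Two assumptions are mine. The bullets are taken in time order, so step 2 precedes ROSC. Body weights are illustrative, because the article gives none.

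**1. Can the stated 20-40 mL/kg be reproduced from the steps?** Add the steps along each path, before any cap:

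| Path | Sum | Total (mL/kg) |
|---|---|---|
| No ROSC, step 2 not triggered | 20 | 20 |
| No ROSC, step 2 triggered | 20 + 10 | 30 |
| ROSC, step 2 not triggered | 20 + (10 to 20) | 30-40 |
| ROSC, step 2 triggered | 20 + 10 + (10 to 20) | 40-50 |

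The first three paths stay within 20-40. Only the last can pass 40, so the full range is 20-50 mL/kg.

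**2. At what weight does each amount reach 2 litres?** Weight = 2000 / (mL/kg):

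- 20 mL/kg: 2000/20 = 100 kg
- 30 mL/kg: 2000/30 = 66.7 kg
- 40 mL/kg: 2000/40 = 50 kg
- 50 mL/kg: 2000/50 = 40 kg

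**3. Volume used before ROSC, and what is left under a cumulative 2 litres:**

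| Weight (kg) | Step 1 only (L) | Steps 1 and 2 (L) | Left after step 1 | Left after steps 1 and 2 |
|---|---|---|---|---|
| 60 | 1.20 | 1.80 | 0.80 L (13.3 mL/kg) | 0.20 L (3.3 mL/kg) |
| 65 | 1.30 | 1.95 | 0.70 L (10.8 mL/kg) | 0.05 L (0.8 mL/kg) |
| 70 | 1.40 | 2.10 | 0.60 L (8.6 mL/kg) | none |
| 80 | 1.60 | 2.40 | 0.40 L (5.0 mL/kg) | none |
| 90 | 1.80 | 2.70 | 0.20 L (2.2 mL/kg) | none |
| 100 | 2.00 | 3.00 | none | none |

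**4. Reading A: the maximum applies only to the step where it is printed.** Steps 1 and 2 together exceed 2 litres above 66.7 kg. Step 1 alone exceeds it above 100 kg.

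**5. Reading B: the maximum is cumulative over all steps.** Two litres is never exceeded. Step 3, however, asks for at least 10 mL/kg more. Without step 2 the minimum total is 20 + 10 = 30 mL/kg, which does not fit above 66.7 kg. With step 2 it is 20 + 10 + 10 = 40 mL/kg, which does not fit above 50 kg, and above 66.7 kg nothing is left at all. Under this reading a total above 40 mL/kg can arise only below 50 kg.

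Above 66.7 kg, therefore, a patient with ROSC cannot receive both the weight-based amounts as written and a total within 2 litres, whether or not step 2 was triggered.

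**The case against.** The strongest reply is that the article largely explains itself.

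- **The maximum.** The step-3 wording refers to total fluid, which naturally includes what has already been infused. The Abstract attaches the 2 litres to the whole infusion, and the treatment-arm summary attaches it to the 20 mL/kg bolus. This stands: Reading B is the better supported. A reader might infer that the protocol directs paramedics past its own limit before ROSC in average-weight adults. The documents do not support that. It requires Reading A together with either the conditional step and a weight above 66.7 kg, or a weight above 100 kg, and no body weight is given from which to call any of these average.
- **The 20 mL/kg statements.** They can be read as the initial bolus. The treatment-arm summary goes on to say that the infusion continues after ROSC, and the closing paragraph ties its figure to CPR, as step 1 does. This softens the contrast with 20-40 mL/kg. It does not remove it, because both places present 20 mL/kg as the intervention without saying that it is only the first part.
- **Conditional steps.** A reader might also infer that the schedule adds up to 40-50 mL/kg for everyone. It does not. That total needs both the temperature trigger and ROSC, and Sample Size expects ROSC in only 40-45% of VF patients. How often step 2 is triggered is unknown. Patients below 34.5°C are excluded at entry, so those enrolled start at or above the trigger value, but the article does not say how many remain above it after 20 mL/kg.
- **An absolute cap on a weight-based amount always truncates it.** True, and the fact that an 80 kg patient can receive at most 2000/80 = 25 mL/kg is not in itself a contradiction. The difficulty is a step that specifies a minimum further amount which the cap leaves partly or wholly undeliverable.
- **Paramedics work from instructions, not from an article.** The randomisation envelopes carry treatment instructions, and the full protocol is not shown. No fault in those unseen documents can be claimed. The conflict is between figures that the article itself prints, so it is not a matter of condensed detail.

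**Conclusion.** The point holds in a limited form. The volume is given as 20-40 mL/kg, as 20 mL/kg (possibly the initial bolus), and as steps totalling 20-50 mL/kg, where anything above 40 needs every step to be given. The scope of the 2-litre maximum is not made explicit where the steps are listed, and neither reading lets the steps and the maximum both stand as written. Reading A allows more than 2 litres before ROSC, under the weight and step conditions shown above. Reading B keeps to 2 litres but makes the post-ROSC minimum undeliverable in full above 66.7 kg.

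The mL/kg sums and weight thresholds follow from the article's figures alone. How many patients are affected depends on body weights, ROSC and the frequency of the temperature trigger, and the article does not allow that number to be worked out. Nor does it support the stronger conclusion that the tested intervention cannot be stated at all: on Reading B most paths lie within the range in the Abstract and aim. This is a correction of wording that should be made, because it bears on a total-volume limit and on the definition of the treatment under test.

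**What to change.** Reconcile the five places: the Abstract, the aim at the end of Background, the treatment-arm summary in Methods/Design, Study Treatments, and the closing paragraph of the Discussion.

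1. State one volume range throughout. Where 20 mL/kg is meant as the initial bolus only, say so.
2. In Study Treatments, state whether the 2-litre maximum covers all steps, including those before ROSC, and make the post-ROSC step consistent with that answer.
3. Describe the tested intervention in the same terms in the aim and in the Discussion.

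The volumes and the scope of the maximum are for the clinical investigators to decide; this review takes no view on them. The cost is wording only, plus a check that the operational instructions agree with it. No patients, visits or analyses are added.

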### Cooled Fluid

The saline will be carried in insulated containers which are changed every shift. A thermometer is housed in this container ensuring the fluid is of the desired temperature.

### Sample Size

This study consists of two parallel clinical trials, separately testing the effect of paramedic cooling during CPR in patients with a shockable rhythm (VF/VT) and non-shockable rhythm (asystole/pulseless electrical activity).

The primary outcome measure for post-VF arrest patients is survival at hospital discharge. Data from the Victorian Cardiac Arrest Register shows that patients who are in ventricular fibrillation on arrival of paramedics have a 40% rate of return of spontaneous circulation, and there was a 50% subsequent survival rate in the previous Melbourne cooling trial [16]. The overall current survival rate based on all participating states is circa 20%. We propose that a rapid infusion of cold IV fluid will increase the rate of return of spontaneous circulation based on laboratory data cited above from 40% to 45%, and that this very early cooling will increase the overall survival rate from 20% to 27%. With 80% power and a type 1 error of 0.05, the study requires a sample size of 603 post VF-arrest patients in each arm (1206 in total).

Randomization of patients with non-VF will occur concurrently. The primary outcome measure for non-VF/VT cardiac arrest patients is also survival at hospital discharge. Currently, the outcome at hospital discharge of these patients is 2% [3]. To demonstrate improved outcomes to 5% (an absolute difference of 3%) requires 653 per group, a total of 1306 patients.

For both studies, secondary outcome measures are the rates of return of spontaneous circulation [23], survival to hospital admission on all patients, and quality of life measured by telephone follow up at 12 months using the Glasgow Outcome Scale Extended (GOSE) [24], EQ-5D [25] and SF-12 Health Survey Summary Score [26]. Analysis will be based on "Intention-to-treat".

### Consent/Ethics

Given that patients in cardiac arrest are unconscious, it is not possible to obtain informed consent prior to randomisation. The Australian National Statement on Ethical Conduct in Human Research [27] is used as the basis for ethical review across the three Australian states involved in this trial. Section 2.3.6 states that a human research ethics committee may grant waiver of consent if (a) involvement in the research carries no more than low risk, and (b) the benefits from the research justify any risks of harm associated with not seeking consent, and (c) it is impracticable to obtain consent and (d) there is no known or likely reason for thinking that participants would not have consented if they had been asked. Sections 4.4.13 requires there be no reason to believe that consent would not be forthcoming were it requested, that the risks of harm are minimized, that the project is not controversial and does not involve significant moral or cultural sensitivities in the community. Section 4.4.13 also requires that the research supports a reasonable possibility of benefit over standard care, that any risk or burden of the intervention to the participant is justified by its potential benefits and that inclusion in the research project is not contrary to the interests of the participant. Section 4.4.14 requires that as soon as reasonably possible, the participant and/or the participant's relatives should be informed of the participant's inclusion in the research and of the option to withdraw from it without any reduction in quality of care.

In addition, enrolment without consent is authorized in Victoria under Section 42A of the Medical Treatment Act. This states that a registered medical practitioner may carry out, or supervise the carrying out of, a medical research procedure on a patient without consent or authorisation if the practitioner believes on reasonable grounds that the treatment is necessary, as a matter of urgency (a) to save the patient's life; or (b) to prevent serious damage to the patient's health. This study meets the intent of this section of the Medical Treatment Act since the treatment (cooling during CPR) is a matter of urgency and has the intention of saving life and preventing serious neurological injury.

Human research ethics committees in the three study states have endorsed the study protocol In Victoria, the Human Research Ethics Committee requested that the Investigators send an explanatory letter to survivors to advise them of enrolment in the study. This letter will be sent about two months after the cardiac arrest to ensure that they have recovered sufficiently to understand the letter. For deceased patients, an explanatory letter will be sent to the next-of-kin also about two months after the cardiac arrest to ensure that they have recovered somewhat from the grief of the death of the relative. If a surviving patient objects to the collection of data, then no further data from that time onwards will be collected. Public engagement has been achieved using media news releases on the trial and information on the trial will also be provided to the public through ambulance service's subscriber newsletters and web sites.

In Western Australia, the University of Western Australia Human Research Ethics Committee requires that that surviving participants are informed of their participation as soon as practicable.

### Data Collection

All data relevant to the study is currently recorded by paramedics immediately after the case as a Patient Care Record. Furthermore, Victoria, Western Australia and South Australia each have a cardiac arrest registry that records the patient, event and outcome data consistent with the Utstein criteria [23] for all OHCAs attended. The Victorian Cardiac Arrest Registry currently conducts a 12-month quality of life follow-up on all survivors. Victorian survivors will therefore be contacted 12 months post cardiac arrest to complete a functional and quality of life outcomes telephone questionnaire.

### Data Safety Management

The Data Safety Monitoring Committee will undertake an interim analysis after 600 post VF and 600 non-VF patients have been enrolled in the study. The study will be stopped if there is a significant difference in the two arms (p < 0.001) at the interim analysis [28]. Given that the majority of patients die at the scene or in the hospital, and recurrent cardiac arrest at any time is possible with standard care, it is not considered appropriate to report every death to the Data Safety Monitoring Group as a serious adverse effect.

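### The stated interim rule (p < 0.001 at 600 patients) gives little protection against survival harm, and almost none in the non-VF trial at the plan's own 2% survival rate

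*Protocol article*

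**What the plan says.** Under Data Safety Management, the protocol article plans an "interim analysis after 600 post VF and 600 non-VF patients have been enrolled in the study". It then gives its one statistical criterion: "The study will be stopped if there is a significant difference in the two arms (p < 0.001) at the interim analysis [28". It names no test, sidedness or interim outcome, and does not say whether a signal in one rhythm group would stop that trial or both. The same section adds that "it is not considered appropriate to report every death to the Data Safety Monitoring Group as a serious adverse effect", because most of these patients die whatever the treatment.

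The Sample Size section treats the two rhythm groups as parallel trials that are tested separately. For non-VF patients, "The primary outcome measure for non-VF/VT cardiac arrest patients is also survival at hospital discharge". On the control rate it says "Currently, the outcome at hospital discharge of these patients is 2% [3", and on size: "To demonstrate improved outcomes to 5% (an absolute difference of 3%) requires 653 per group, a total of 1306 patients". The VF trial assumes survival of 20% in controls and 27% with cooling, and gives its size as follows: "With 80% power and a type 1 error of 0.05, the study requires a sample size of 603 post VF-arrest patients in each arm".

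**The concern.** A strict threshold at a single early look has a clear purpose for benefit: it limits early false claims and leaves the final type 1 error almost untouched. That reason does not carry over to harm. There, the same strictness only makes a harmful effect harder to act on.

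The non-VF trial is the difficult case. With 2% survival there are so few survivors at the interim that even their complete loss in one arm may not reach p < 0.001. Patients are enrolled without prior consent, under an ethical framework that the article describes as requiring risks to be minimised. It therefore matters whether the one rule on paper could respond to a loss of survival.

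**Working it through.** **Inputs.** Interim at 600 patients per rhythm group, so about 300 per arm (Data Safety Management). Control survival 2% in non-VF and 20% in VF (Sample Size). Threshold p < 0.001.

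**Assumptions.** Two-sided test, survival to discharge as the interim outcome, equal arms, and outcomes complete for all 600.

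**The plan's own figures.** The two-proportion formula with two-sided 0.05, 80% power and continuity correction gives 653 per group for 2% against 5%, and 603 for 20% against 27%. Both match the article. Without the correction the results are 588 and 575. The plan's inputs are therefore read correctly, and two-sided testing is consistent with its sizing.

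**Non-VF, expected counts.** 300 × 0.02 = 6 control survivors. Suppose no cooled patient survives.
- Fisher: 2 × C(300,6)/C(600,6) = 0.030.
- Pooled z: 0.02 / √(2 × 0.01 × 0.99 / 300) = 2.46, p = 0.014.
- With continuity correction: p = 0.040.

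**Non-VF, what it takes to cross with 0 cooled survivors.**
- 10 against 0: Fisher p = 0.0018.
- 11 against 0: Fisher p = 0.00089, pooled z p = 0.00082.
- With continuity correction, 13 are needed (p = 0.00077).

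If cooled survival is truly zero, the chance of a harm stop is P(X ≥ 11), X ~ Bin(300, 0.02), which is 0.041. With continuity correction it is P(X ≥ 13) = 0.008.

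**Chance of a harm stop in general.** Let c*(t) be the smallest control count that crosses when t cooled patients survive. Then P(stop) = Σ P(T = t) × P(C ≥ c*(t)), with both counts binomial. For Fisher, c*(0) = 11, c*(1) = 14 and c*(2) = 17. The last two columns give the same sum for a one-sided p < 0.025 harm guideline at the same look.

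| True survival, control to cooled | Stated rule, Fisher | Stated rule, pooled z | Guideline, Fisher | Guideline, pooled z |
|---|---|---|---|---|
| Non-VF 2% to 0% | 4.1% | 4.1% | 56% | 85% |
| Non-VF 2% to 0.5% | 1.0% | 1.0% | 23% | 37% |
| Non-VF 2% to 1% | 0.25% | 0.26% | 9% | 16% |
| VF 20% to 15% | 3.7% | 4.5% | 33% | 36% |
| VF 20% to 13% | 14% | 16% | 60% | 64% |
| VF 20% to 10% | 52% | 56% | 92% | 94% |
| No effect, non-VF | 0.01% | 0.02% | 1.2% | 2.5% |
| No effect, VF | 0.04% | 0.05% | 2.0% | 2.5% |

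**Why the guideline depends on the test.** In non-VF, pooled z flags at 4 against 0 (one-sided p = 0.022), and P(X ≥ 4) = 0.85. Fisher gives 0.062 at 4 against 0 and 0.031 at 5 against 0, so it first flags at 6 against 0 (p = 0.015), and P(X ≥ 6) = 0.56.

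**VF at expected counts.** Against 60 of 300 controls, pooled z needs 31 or fewer cooled survivors (p = 0.00096; 32 gives 0.0015). Survival must be roughly halved.

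**Sensitivity to the 2%.** If no cooled patient survived and true control survival were higher, the stated rule would fire 29% of the time at 3%, 66% at 4% and 89% at 5% (Fisher).

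**The case against.** The section is a few sentences in a condensed journal article. It names a monitoring committee and does not say that the committee may act on nothing else. Harm guidance, safety outcomes and per-trial application usually sit in a charter or full protocol, which is not shown. A single stringent threshold is conventional, the article cites a reference for it, and nothing here is miscalculated. All of this stands, and it limits the point to how the stated rule performs. A charter could add to that rule but would not make it more sensitive.

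Several stronger readings are tempting and are not supported:
- **The rule cannot stop the non-VF trial for harm.** That is true at the expected counts of 6 against 0, but chance can still carry the result across, with a probability of up to about 4%.
- **This look is the only survival check, so there is no working safety boundary.** The sentence on deaths declines case-by-case reports as serious adverse effects. It does not withhold deaths from the committee, and the Data Collection section says registries in all three states record outcomes.
- **A harmful effect would run to full enrolment.** The rule speaks of stopping the study. A VF signal might therefore stop both trials, and the VF rule fires 52–56% of the time if survival halves.

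It is also fair to say that much of the weakness in non-VF comes from scarce events. A looser threshold repairs this only in part: for survival halved from 2% to 1%, the guideline flags 9–16% of the time.

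**Conclusion.** The point holds as a statement about the rule on the page. At the plan's 2% non-VF survival, that rule would miss a complete loss of survival in the cooled arm about 96% of the time, and more often with a continuity correction. In the VF trial it responds about half the time to a halving of survival and seldom to smaller falls.

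The non-VF conclusion does not depend on which test was meant. It does rest on the 2% rate, and on a two-sided comparison of discharge survival with about 300 per arm and complete outcomes. If control survival were 3% or more, the rule would do better against total loss.

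This is a cheap improvement and not an error that must be corrected. The final analysis is unaffected, and other safety review may exist outside the article.

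**What to change.** Keep p < 0.001 for benefit. At the same look, add a non-binding harm guideline for the monitoring committee, applied within each rhythm trial and with the test named; one-sided p < 0.025 on survival to discharge is an example. State the interim outcome, and whether a signal in one rhythm group bears on the other. Because survivors are scarce in non-VF, also show the committee return of spontaneous circulation by arm. It is already a secondary outcome, at about 40% in VF. The article gives no non-VF rate, so its power there cannot be stated.

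The cost is wording in the protocol and the committee's charter. A non-binding harm guideline spends no efficacy alpha and adds no patients or data. The downside is a false harm flag when there is no effect: about 1% (Fisher) to 2.5% (pooled z) in non-VF, and 2% to 2.5% in VF. The committee would weigh such a flag and not be bound by it.
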